## Detailed description

### Usual care group (control)

Participants randomly assigned to the usual care group will receive normal hospital care, which includes physical rehabilitation when needed.

### Intervention group (training)

The intervention will consist of a multicomponent exercise training programme [46], which will be composed of supervised progressive resistance exercise training, balance-training, and walking for 5–7 consecutive days. During the training period, patients will be trained in 20 min sessions twice a day (morning and evening).

The supervised multicomponent exercise training programme will be comprised of upper and lower body strengthening exercises, tailored to the individual’s functional capacity, using weight machines and aiming for 2–3 sets of 8–10 repetitions at an intensity of 30–60 % of 1RM (Matrix, Johnson Health Tech, Ibérica, S.L. Torrejón de Ardoz, Madrid, Spain) combined with balance and gait retraining exercises that progressed in difficulty and functional exercises, such as rises from a chair. The second part of the session will consist of functional exercises such as knee extension and flexion, hip abduction, balance movements, and daily walking in the hospital. A minimum of 2 days elapsed between consecutive training sessions. The resistance exercises focused on the major upper and lower limb muscles. Each resistance training session will include 2 exercises for the leg extensor muscles (bilateral leg extension and bilateral knee extension muscles) and 1 exercise for upper limbs (seated bench press). During the progressive resistance training, instruction will be provided to the participants to perform the exercises at a high velocity of motion. However, care will be taken to ensure that exercises were executed with correct form. In each session, subjects will perform a specific warm-up with one set of very light loads for the upper and lower body. Balance and gait retraining exercises that progressed in difficulty will be also implemented: semi-tandem foot standing, line walking, stepping practice, walking with small obstacles, proprioceptive exercises on unstable surfaces (foam pads sequence), and altering the base of support and weight transfer from one leg to the other. One experienced physical trainer will carefully supervise all training sessions. The training sessions will last for approximately 40 min. The approximate duration of each part of the training will be: 5 min of warm-up, 10 min balance and gait retraining, 15 min of resistance training, and five minutes of stretching (cool-down). The training protocol is shown in Table 2. Participants and their family members will be carefully familiarized with the training procedures in advance.

**Table 2 Tab2:** Intervention group exercises

	Exercise	Day 1	Day 2	Day 3	Day 4	Day 5	Day 6*	Day 7*
Morning	Rises from a chair	1×5	1×10	2×10	3×10	3×8	3×8	3×8
	Leg press	1RM + 1×10 (30 % 1RM)	2×10 (30 % 1RM)	3×10 (40 % 1RM)	3×10 (50 % 1RM)	3×8 (60 % 1RM)	3×8 (60 % 1RM)	3×8 (60 % 1RM)
	Chet press	1RM + 1×10 (30 % 1RM)	2×10 (30 % 1RM)	3×10 (40 % 1RM)	3×10 (50 % 1RM)	3×8 (60 % 1RM)	3×8 (60 % 1RM)	3×8 (60 % 1RM)
	Leg extension	1RM + 1×10 (30 % 1RM)	2×10 (30 % 1RM)	3×10 (40 % 1RM)	3×10 (50 % 1RM)	3×8 (60 % 1RM)	3×8 (60 % 1RM)	3×8 (60 % 1RM)
Afternoon	Leg extension (0,5 – 1,0 Kg)		2×10	2×10	2×10	2×10	2×10	2×10
	Leg flexion (0,5 – 1,0 Kg)		2×10	2×10	2×10	2×10	2×10	2×10
	Hip abduction (0,5 – 1,0 Kg)		2×10	2×10	2×10	2×10	2×10	2×10
	Hand grip ball		2×10	2×10	2×10	2×10	2×10	2×10

*In case that the patient is still hospitalized

### Outcome measures

#### Primary outcome

The primary outcome measure is the change in functional and cognitive status during the study period. The functional capacity of patients will be evaluated by the Short Physical Performance Battery (SPPB) [47], which evaluates, balance, gait ability, and leg strength using a single tool. The total score will range from 0 (worst) to 12 points (best). The SSPB test has been shown to be a valid instrument for screening frailty and predicting disability, institutionalization, and mortality. A total score of less than 10 indicates frailty and a high risk of disability and falls. One-point change in the score has clinical relevance [48, 49]. Loss of handgrip of the dominant hand is a useful tool for the measurement of functional capacity. It is a strong predictor of disability, morbidity, and mortality as well as one of the components of Fried’s frail phenotype. Furthermore, the functional status of patients will also be assessed before measurements with the Barthel Index, an international and validated tool of disability. The scores range from 0 (severe functional dependence) to 100 (functional independence) [50]. Gait ability will be assessed using the 6-metre gait velocity test (GVT). Starting and ending limits will be marked on the floor with tapelines for a total distance of 8 m. Participants will be instructed to walk in their self-selected usual pace for two attempts. The results of both trials will be averaged to obtain a single value. The first and last metre, considered the warm-up and the deceleration phases, respectively, will not be included in the calculations of the gait assessment. Dual task conditions (gait evaluation during the simultaneous performance of a cognitive motor action) have recently been recognized as a sensitive assessment method for interactions between cognition, gait, falls and frailty. Changes of gait parameters (i.e., gait velocity and gait variability) while performing a dual task test (dual task cost) could be early predictors of falls risk (50) and useful tools for functional evaluations in frail elderly patients. Exercise can modify dual task cost and consequently fall risk and functional capacity (31). The dual-task paradigm [51] will be used in the 6-m habitual gait velocity test (GVT). Two trials will be performed to assess the gait velocity while performing a verbal or counting task (verbal GVT and counting GVT, respectively). During the verbal dual-task condition (verbal GVT), we will measure the gait velocity while participants are naming animals aloud. During the arithmetic dual-task condition (counting GVT), we will assess the gait velocity while participants are counting backward aloud from 100 by ones. The cognitive score will be measured by counting the number of animals named (dual-task with verbal performance) or determining how many numbers were counted backward (dual-task with arithmetic performance). Isometric upper (right hand grip) and lower limb (right knee extensors and hip flexors) muscle strength will be measured using a manual dynamometer. Maximal dynamic strength will be assessed using the 1RM test in the bilateral leg press, knee extension and bench press exercises using exercise machines (Exercycle, S.L., BH Group, Vitoria, Spain). In the first assessment, the subjects will warm up with specific movements for the exercise test. Each subject's maximal load will be determined in no more than five attempts, with a 3-min recovery period between attempts. After determination of the 1RM values, the subjects will perform ten repetitions at maximal velocity at intensities of 50 % of 1RM to determine the maximum power (w) and the loss of power during the ten repetitions in the leg press machine. The power will be recorded by connecting a velocity transducer to the weight plates (T-Force System, Ergotech, Murcia, Spain). During all neuromuscular performance tests, a strong verbal encouragement will be given to each subject to motivate them to perform each test action as optimally and rapidly as possible. Qualified fitness specialists will individually monitor and carefully supervise all training sessions and provide instruction and encouragement during all sessions. Distribution of the training sessions throughout the day should minimize cumulative fatigue and help to maintain adherence. Adherence to the exercise intervention programme will be documented in a daily register of sessions. Changes in cognitive-affective status after the intervention will be measured using the Mini Mental State Examination, Yesavage GDS and Trail Making Test (Table 3).

**Table 3 Tab3:** Collected variables

1. Baseline measurements: Outcomes measures will be collected on the test day written in an information sheet.	
1.1. Individual characteristics:	
Demographic variables	Information regarding the age and the gender of the patients will be collected.
Functional status	Reflects the ability of the patient for performing activities of daily living, as well as the capacity to relate with others and participating in society. It will be measured with the Barthel Index.
Functional capacity	SPPB, Gait velocity, Handgrip, dual tests.
Cognitive function	Highlights cognitive impairments that might interfere with self-care and independence in elderly patients. In the present study, we will use the Mini Mental State Examination, and the Trail Making Test as executive function parameters, as well as the Confusion Assessment method for delirium evaluation, and the Geriatric depression Scale of Yesavage as an indicator of psychosocial status.
Caregiver burden	Will be measured through Zarit scale.
Nutritional status	Indicates malnutrition risk in elderly patients. In addition to the weight and height data, information related to factors that increase the risk of malnutrition will be collected. These will be measured via MNA test.
Quality of Life	Evaluates the individual’s social well being, due to its easiness in administration, validity and reliability, the EuroQol-5D is one of the questionnaires with largest diffusion and validity.
Geriatrics syndromes	Characterised by the simultaneous presence of illnesses, clinical and functional conditions that can usually lead to incapacity. The specific presence of immobility, incontinence, constipation, pressure ulcers, cognitive impairment, delirium, depressive tendencies, falls, insomnia, visual impairments, hearing impairments, malnutrition, dysphagia, and pain.
Comorbidity	Will be measured by means of Cumulative Illness Rating Scale-Geriatrics (CIRS-G).

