### Statistics and sample size

The required simple size to detect a difference of 15 % in the frequency of patients that get at discharge a functional improvement greater than 10 points in Barthel Index is 161 patients in each group. Assuming a loss of 15 % of patients in the follow-up, we fixed a final sample size of 185 patients per group.

In an initial descriptive analysis, for qualitative variables we will calculate frequencies and confidence intervals, and for continuous variables, statistics of central tendency and dispersion such as means, standard error and confidence intervals or median and interquartile range. In order to assess the extent of the therapeutic effect, we will compute for every patient the difference between final and initial level of the outcome variables. Normality of continuous variables will be checked graphically and through K-M and Shapiro-Wilk tests, and their differences between groups by means of parametric tests (T-Tests, ANOVA) or non-parametric tests (Mann–Whitney U, Kruskal- Wallis). A Bonferroni post-hoc test will be used to evaluate statically significant (*p* < 0.05) group and time differences. Associations between clinical and biomechanical tests will be reported by their correlation coefficient (r value), level of significance (p value), and the amount of variance explained (r2 value). Values of r will be used to indicate small (r = 0.10), medium (r = 0.30), and large (r = 0.50) size correlations (i.e., effect size). Finally, the relationship between qualitative variables will be assessed through χ^2^ and Fisher exact tests. The level of statistical significance will be 0.05. Data will be analyzed with SPSS package 21.0

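### The primary outcome is an open set of about 18 measures with no named variable, visit or success rule, no error control across measures, and no link to the sample-size endpoint

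*Protocol article*

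**What the plan says.** The Primary outcome section opens: "The primary outcome measure is the change in functional and cognitive status during the study period". It then describes, under the same heading, a long series of tests:

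- SPPB, and the Barthel Index ("the functional status of patients will also be assessed before measurements with the Barthel Index").
- Usual-pace gait velocity, and two dual-task velocities ("Two trials will be performed to assess the gait velocity while performing a verbal or counting task").
- A score from each dual task ("The cognitive score will be measured by counting the number of animals named", or the count of numbers recited backward).
- Isometric force of handgrip, knee extensors and hip flexors.
- Three one-repetition maxima ("Maximal dynamic strength will be assessed using the 1RM test in the bilateral leg press, knee extension and bench press exercises").
- Maximum power and loss of power on the leg press.
- Three cognitive-affective scales ("Changes in cognitive-affective status after the intervention will be measured using the Mini Mental State Examination, Yesavage GDS and Trail Making Test").

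Table 1 schedules these tests at baseline (T1) and at three later visits (T2 to T4). The Statistics and sample size section computes a final-minus-initial difference for the outcome variables and states: "The level of statistical significance will be 0.05". Its only multiplicity step begins "A Bonferroni post-hoc test will be used to evaluate" and concerns differences by group and time. The same section sizes the trial at 161 per group, raised to 185, for a 15% difference in the share of patients who gain more than 10 Barthel points at discharge.

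**The concern.** A primary outcome has to tell the reader in advance which single result, or which stated combination of results, decides whether the trial succeeded. Here the text gives two domains and many instruments. It does not say which instrument decides, at which visit, or whether one positive measure is enough. The time frame is loose too: the outcome section refers to the whole study period, the analysis to a final level, and the sample size to discharge.

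The sample-size endpoint does not close the gap. The Barthel Index appears in the outcome section as one tool among many, and the responder definition of more than 10 points does not appear there at all.

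The Discussion says that a positive result may justify changing how older medical patients are cared for in hospital. That conclusion should not rest on whichever of many measures happens to fall below 0.05.

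**Working it through.** **The plan's own figure.** The plan gives neither power nor a control-group rate, so 161 cannot be derived from its stated inputs alone. It is attainable. Assume two-sided 0.05, 80% power and 29% versus 44%:

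n = [1.960 × √(2 × 0.365 × 0.635) + 0.842 × √(0.29 × 0.71 + 0.44 × 0.56)]² / 0.15² = 160.5, rounded up to 161.

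The step to 185 matches 161 × 1.15 = 185.15. So 161 is consistent with one test of one binary endpoint at an unadjusted 0.05.

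**Count of measures under the Primary outcome heading.** SPPB and Barthel (2), gait velocities (3, total 5), dual-task scores (2, total 7), isometric forces (3, total 10), one-repetition maxima (3, total 13), power measures (2, total 15), MMSE, Yesavage GDS and Trail Making (3, total 18). Handgrip is mentioned twice and counted once.

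**Narrower count from Table 3.** Table 3 places Barthel under functional status, and SPPB, gait velocity, handgrip and the dual tests under functional capacity. MMSE, Trail Making and Yesavage GDS come under cognitive function. With two dual tests this makes nine. The Confusion Assessment Method also stands in that row but is listed as a secondary outcome, so it is left out.

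**Chance of at least one false positive at one visit, no true effect, each test at two-sided 0.05.**

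- Independent tests: 1 − 0.95^k. For k = 18 this is 0.603, and for k = 9 it is 0.370.
- Correlated tests: Zᵢ = √r·G + √(1 − r)·Eᵢ, with G and Eᵢ independent standard normal. The result is P(max|Zᵢ| > 1.96). The values of r are assumed, because the document gives none.

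| Measures | independent | r = 0.3 | r = 0.5 | r = 0.7 |
|---|---|---|---|---|
| 18 | 60% | 51% | 40% | 28% |
| 9 | 37% | 33% | 27% | 20% |

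These count false positives in either direction. Counting only those that favour exercise, 18 measures give 37% if independent (1 − 0.975^18 = 0.366) and 26%, 20% and 14% at the three correlations, against a nominal 2.5%.

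**Effect of the three follow-up visits.** With every visit at an uncorrected 0.05, 18 × 3 = 54 tests give 1 − 0.95^54 = 0.937 if independent. The range is 51 to 85% for assumed correlations of 0.3 to 0.7 between measures and 0.5 to 0.7 between visits. If the Bonferroni step is credited across the three visits (0.05/3 per test), the figures are 1 − (1 − 0.05/3)^54 = 0.597 if independent and 24 to 49% over the same correlations.

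**What control across measures would require.** Bonferroni at one visit needs 0.05/18 = 0.0028 per test for 18 measures, or 0.05/9 = 0.0056 for nine. One pre-named variable at one visit keeps the error at 0.05.

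**The case against.** Several points on the other side have force.

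- **The count of 18 is one reading.** The section mixes outcome definition with test methods and training supervision. Table 3 puts isometric force and muscle power under a separate heading for intervention measurements. This stands, and is why the nine-measure row is given. It reduces the error without removing the problem.
- **The measures are correlated.** SPPB itself covers balance, gait and leg strength. The gait velocities come from one test, and the strength and power measures from related machine tests. Independence is therefore an upper limit, not the expected case.
- **A reader might infer a 94% false-positive risk over 54 tests.** The document does not support that as the expected figure. The Bonferroni step can be read as covering visits, and the analysis describes one final-minus-initial difference per patient. The 94% is a worst case.
- **A reader might add that practice alone favours the intervention arm on the one-repetition maxima,** since those exercises are trained. That is a question of what the tests measure, not of false positives, and the document gives no size for it. The stated makes of machine also differ between training and testing. It is not part of this point.
- **A statistical analysis plan may exist and may hold a multiplicity rule.** That is possible. But choosing the primary variable belongs in the protocol, and this protocol makes the choice as an open set.

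**Conclusion.** The point holds. As written, the primary claim has no named variable, visit or success rule and no error control across measures. The one endpoint used to size the trial is not identified as primary.

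If any one measure at one visit can count as success, the false-positive chance is about 28 to 60% for 18 measures and about 20 to 37% for nine. These ranges run from an assumed correlation of 0.7 to independence. Even the lowest value is about four times the nominal 5%.

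A reader might go further and call a false positive likely. That is literally true only for 18 measures at low correlation, so well above nominal is the supportable wording. The figures assume no true effect on any measure and two-sided tests. They also assume that a single positive measure would be reported as success, which the text permits but does not state.

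**What to change.** Name one primary variable at the discharge assessment (T2), tested at two-sided 0.05, and make it agree with the sample-size endpoint. There are two ways:

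1. Adopt the endpoint already used for sizing, a Barthel gain of more than 10 points at discharge, and state it in the Primary outcome section.
2. Choose another instrument, such as SPPB at T2, and restate the sample-size justification for it at the existing 370 patients.

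Label the other measures and the T3 and T4 results as secondary or exploratory. If some are to support confirmatory claims, state a multiplicity procedure for them. One example is a fixed testing order behind the primary that includes one cognitive measure; other valid procedures would serve as well.

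Cost: fewer results can be called confirmatory. The second route also needs a new sample-size statement. Because the Trial status section says that recruitment is open, either route is a dated amendment to the primary outcome of a running trial. It should be made before any outcome data are compared by group.

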**Fig. 1 Fig1:**
[figure not shown]
Flow diagram of the study protocol

**Table 1 Tab1:** Time of measurement of the different variables on the participants of the study

Measurement	T1 Baseline	T2 After training or control period	T3 1-month	T4 3-months
Categorical scale of pain	X	X	X	X
Barthel Index	X	X	X	X
Geriatric depression Scale of Yasavage	X	X	X	X
Mini-Mental State Examination (MMSE)	X	X	X	X
Short Physical Performance Battery (SPPB)	X	X	X	X
Gait Velocity Test (GVT)	X	X	X	X
Dual-task (verbal and counting GVT)	X	X	X	X
Maximal isometric force of handgrip, knee extension and hip flexion	X	X	X	X
1RM (Leg press, Chest press and Knee extension)	X	X	X	X
Muscle power at 50 % 1RM in Leg press	X	X	X	X
Confusion Assessment Method (CAM)	X	X	X	X
Quality of Life (EQ-5D)	X	X	X	X
Geriatrics syndromes	X	X	X	X
Isaacs set test	X	X	X	X
Trail Making Test (TMT)	X	X	X	X
Laboratory parameters	X			
Diseases considered grouped by ACG of Salisbury and CIE-10 codes	X			
Cumulative Illness Rating Scale for Geriatrics (CIRS-G)	X			
Zarit Scale	X			
Falls	X	X	X	X
Mini Nutritional Assessment (MNA)	X			

Adverse events, including muscle pain, fatigue, and general aches and pains will be recorded by the training and testing staff and by self-report during the study period. We will also record the number of falls during the study and for one year prior to admission.

This study has been approved by the Navarra Clinical Research Ethics Committee (Pyto 23/2014).

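### The dual-task cognitive score is a raw count over a fixed-distance walk, so at an unchanged response rate it falls as gait speed rises; it should be analysed as a rate

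*Protocol article*

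**What the plan says.** The relevant text is in the Protocol article under Outcome measures, Primary outcome. The spoken task is added to the ordinary walking test: "The dual-task paradigm [51] will be used in the 6-m habitual gait velocity test (GVT"). The walkway is fixed: "Starting and ending limits will be marked on the floor with tapelines for a total distance of 8 m", with the first and last metre left out of the gait calculation. Pace is free: "Participants will be instructed to walk in their self-selected usual pace for two attempts". In one condition patients name animals; in the other, "we will assess the gait velocity while participants are counting backward aloud from 100 by ones". Gait velocity is measured in both.

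The scoring rule for the spoken part is then given: "The cognitive score will be measured by counting the number of animals named (dual-task with verbal performance) or determining how many numbers were counted backward". The article does not fix the duration of the task, divide the count by time, or take a seated reference count.

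Table 1 schedules the test, listed as "Dual-task (verbal and counting GVT"), at all four visits. Under Statistics and sample size, the general analysis rule is that "we will compute for every patient the difference between final and initial level of the outcome variables", and these differences are compared between groups.

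Two other places limit what the count is used for. The Primary outcome section names the Mini-Mental State Examination, the geriatric depression scale and the Trail Making Test as the measures of cognitive-affective change. Table 3 places the dual tests under functional capacity, not under cognitive function.

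**The concern.** When distance is fixed and pace is free, a faster patient has less time to speak. A raw count therefore carries two quantities, how quickly the patient produces responses and how long the walk lasts, and it cannot separate them. Both raise the count, but a longer walk is a worse gait result.

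Randomisation does not remove the problem, because walking time is something the intervention is meant to change. The programme trains walking, balance and leg power, and the protocol itself expects exercise to alter dual-task cost. If gait improves in the trained arm, walking time shortens there and the final-minus-initial count is pulled down in that arm only. A control patient who slows down gains count without any cognitive change. At stake is a between-group comparison of this score that could understate a real gain in response rate, or show a loss where there is none.

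**Working it through.** **Inputs from the Protocol article.** Distance D is fixed: 6 m timed within 8 m marked. Pace is self-selected. The score is a count. The analysis quantity is final minus initial. The protocol states no figure for this score, so there is nothing to reproduce.

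**Inputs assumed.** The protocol gives neither gait speeds nor response rates. Speeds of 0.5 or 0.6 m/s before and 0.6 to 0.8 m/s after are used for illustration, with response rates r of 0.5 to 1.5 items per second, unchanged between visits.

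**Identity.** Walking time T = D/v. Count C = r × T = r × D/v. At unchanged r, the relative change in count is C1/C0 − 1 = v0/v1 − 1; r and D cancel. The rate would have to rise by v1/v0 − 1 for the count to stay level.

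**Results over 6 m at r = 1 item per second.**

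| Speed, m/s | Time, s | Count | Change in count | Rate rise needed to break even |
|---|---|---|---|---|
| 0.5 to 0.6 | 12.0 to 10.0 | 12.0 to 10.0 | −17% | 20% |
| 0.6 to 0.7 | 10.0 to 8.6 | 10.0 to 8.6 | −14% | 17% |
| 0.5 to 0.7 | 12.0 to 8.6 | 12.0 to 8.6 | −29% | 40% |
| 0.6 to 0.8 | 10.0 to 7.5 | 10.0 to 7.5 | −25% | 33% |

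**In items.** The smallest loss in this range is 0.5 × (10.0 − 8.57) = 0.7 items and the largest is 1.5 × (12.0 − 8.57) = 5.1 items over 6 m. If the count covers 8 m, multiply by 8/6: 1.0 to 6.9 items. The percentages are the same for either distance and for every rate.

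**Opposite direction.** A patient who slows from 0.6 to 0.5 m/s at an unchanged rate gains 0.6/0.5 − 1 = 20% in count.

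**After the change to a rate.** C/T = r. At unchanged r the change is zero for every speed pair, provided count and time refer to the same stretch of walkway.

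**The case against.** The strongest reply is that the count matters little in this trial. The dual-task result that the protocol describes is mainly gait velocity, and dual-task cost is introduced there as a change in gait parameters. A patient who slows down to talk is visible in the velocity. The count appears neither among the named measures of cognitive-affective change nor in the cognitive function row of Table 3. This stands, and it limits the point to one sub-score.

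A reader might go further and infer that a gait benefit would be reported as cognitive decline in the trial's primary result. The document does not support that. The count is labelled a cognitive score and sits under the primary-outcome heading, but nothing says that it will be compared between arms, alone, as the evidence on cognition. A reader might also infer that a faster patient must score worse. That holds only if the response rate does not rise in proportion to speed; with a large enough rise, the count stays level or increases.

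A third reply is that converting a count to a rate is a detail for an analysis plan, or for the source cited for the paradigm, neither of which is available here. It carries some weight: the sentence says what is counted, not every step of the analysis. But the article is not silent. It states a scoring rule, that rule is a raw count, and its general analysis rule takes differences of outcome variables as measured. Followed as written, it gives the confounded score.

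Finally, the sizes rest on assumed speeds. That is so. The direction and the formula do not.

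**Conclusion.** The point holds in a limited form. As defined, the dual-task cognitive score depends on walking time and is biased against the arm whose gait improves. The bias in the count is v0/v1 − 1: about −14% to −29% for gains of 0.1 to 0.2 m/s from 0.5 or 0.6 m/s. This assumes those speeds, which the protocol does not give, and a response rate that does not change.

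Dual-task gait velocity, the SPPB, the Barthel Index, the Mini-Mental State Examination, the geriatric depression scale and the Trail Making Test are not affected. The sample size rests on the Barthel Index and is not touched. The weight is moderate: one secondary-level component, but with a built-in direction, a size that could matter, and an easy correction.

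**What to change.** Define the score as responses per second of walking: the number of animals named, or numbers counted, divided by the walking time of the same trial. State whether the counted stretch is the middle 6 m or the full 8 m, and take the time over that same stretch. Report and interpret the rate beside dual-task gait velocity, and do not analyse the raw count alone.

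If the 6 m stretch is used, walking time needs no new measurement, because it is 6 m divided by the recorded velocity. The change is a sentence or two in the protocol or analysis plan.

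There are two costs. First, counting and timing must be aligned. If responses are counted over the whole walkway and only the middle is timed, the ratio mixes segments, so assessors may need a rule for when counting starts and stops. Second, a rate over a short walk is noisy. The text appears to give one trial per dual-task condition, and the averaging of two attempts is stated only for the ordinary walk, so averaging cannot be assumed to reduce that noise.
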